## Abstract

**Background:**

The primary objective of this randomised controlled trial (RCT) is to establish the effectiveness of a novel online quality of life (QoL) intervention tailored for people with late stage (≥ 10 episodes) bipolar disorder (BD) compared with psychoeducation. Relative to early stage individuals, this late stage group may not benefit as much from existing psychosocial treatments. The intervention is a guided self-help, mindfulness based intervention (MBI) developed in consultation with consumers, designed specifically for web-based delivery, with email coaching support.

**Methods/design:**

This international RCT will involve a comparison of the effectiveness and cost-effectiveness of two 5-week adjunctive online self-management interventions: Mindfulness for Bipolar 2.0 and an active control (Psychoeducation for Bipolar). A total of 300 participants will be recruited primarily via social media channels. Main inclusion criteria are: a diagnosis of BD (confirmed via a phone-administered structured diagnostic interview), no current mood episode, history of 10 or more mood episodes, no current psychotic features or active suicidality, under the care of a medical practitioner. Block randomisation will be used for allocation to the interventions, and participants will retain access to the program for 6 months. Evaluations will be conducted at pre- and post- treatment, and at 3- and 6- months follow-up. The primary outcome measure will be the Brief Quality of Life in Bipolar Disorder Scale (Brief QoL.BD), collected immediately post-intervention at 5 weeks (T1). Secondary measures include BD-related symptoms (mania, depression, anxiety, stress), time to first relapse, functioning, sleep quality, social rhythm stability and resource use. Measurements will be collected online and via telephone assessments at baseline (T0), 5 weeks (T1), three months (T2) and six months (T3). Candidate moderators (diagnosis, anxiety or substance comorbidities, demographics and current treatments) will be investigated as will putative therapeutic mechanisms including mindfulness, emotion regulation and self-compassion. A cost-effectiveness analysis will be conducted. Acceptability and any unwanted events (including adverse treatment reactions) will be documented and explored.

**Discussion:**

This definitive trial will test the effectiveness and cost-effectiveness of a novel QoL focused, mindfulness based, online guided self-help intervention for late stage BD, and investigate its putative mechanisms of therapeutic action.

**Trial registration:**

ClinicalTrials.gov: NCT03197974. Registered 23 June 2017.

**Electronic supplementary material:**

The online version of this article (10.1186/s12888-018-1805-9) contains supplementary material, which is available to authorized users.

## Background

Bipolar disorder (BD) is a serious mental disorder affecting approximately 4% of the adult population [1]. Large prospective and cross-sectional studies suggest that about 50% of people diagnosed with BD can be considered ‘late stage’ (experiencing ≥10 mood episodes) [2, 3]. This ‘late stage’ group carry a disproportionate burden of functional impairment and chronic depressive symptoms [3], double the risk of relapse, and significantly impaired functioning and QoL [3]. Stage of illness impacts prognosis, course outcome and treatment needs. There is evidence that responsivity to pharmacotherapy varies by stage of illness, and there is similar evidence for some psychotherapies [4].

### Adjunctive psychological treatment for late stage BD

Current adjunctive psychological treatments for BD emphasise relapse-prevention by monitoring triggers and avoiding stress. However, this may be detrimental to self-esteem in late stage BD where relapse is often unrelated to discernible life events [5]. Indeed, having experienced more than 12 episodes of BD has been found to predict a *negative* response to cognitive behaviour therapy (CBT) [6]. In late stage BD, therefore, symptom-focused treatments may be less beneficial than approaches that recognise the unavoidability of suffering, emphasise redefinition of life goals, and prioritise QoL outcomes [7, 8]. These priorities are consistent with the “third wave” [9] or contextual cognitive-behavioural therapies [10], which typically prioritise *mindfulness* - an awareness of present experience and a non-judgemental stance towards that experience [11].

Empirical research into mindfulness based interventions (MBIs) for BD has primarily explored face-to-face delivery, with Mindfulness Based Cognitive Therapy (MBCT) [12] the primary target of investigation. Studies report benefits for BD symptoms and associated psychological variables, in particular anxiety and emotion regulation [13]. Beneficial effects of MBIs in other domains have been reported including QoL [14], well-being, stress and rumination [15]. Evidence for effects on relapse prevention is limited: one study found no benefits for bipolar relapse [16], while another found decreased depressive relapse in a bipolar subset of people with recurrent depression [17]. A recent meta-analysis on the efficacy of MBIs as an adjunctive treatment for BD showed significantly beneficial effects on depressive and anxiety symptoms in within-group analysis [18]. However, this significance was not observed in comparison with control groups, limiting conclusions due to the small number of controlled studies and small sample sizes. Furthermore, studies examining mindfulness as part of another treatment modality (e.g., Acceptance and Commitment Therapy; ACT) were excluded from their review, as were short-duration (< 3 week) interventions and self-help interventions delivered online [8]. A further limitation of studies to date is their focus on symptom/distress reduction, which is at odds with the main goals of CCBT approaches [19]. Mechanisms of action of such approaches are still unclear, as process variables (e.g., mindfulness, acceptance, self-compassion) have not been examined in mediational analyses. In summary, further clinical trials are needed to determine the efficacy of MBIs for improving QoL in BD and understanding their mechanisms of action.

### Maximising access to adjunctive psychological treatments

Web-based psychological interventions have great potential to complement treatment as usual and overcome barriers to accessing psychological assistance for BD (e.g., cost, time, trust in professionals) [20]. Such interventions have demonstrated short- and long-term benefits for a range of mental disorders [21] and are acceptable to people with BD [22, 23]. There is a lack of consistent evidence regarding effectiveness of web-based psychological interventions for BD as most trials to date have focused on feasibility. Recent findings confirm that MBIs are effectively delivered via the web [24], including for mood disorder populations [25]. The benefits of low intensity web-based interventions are yet to be widely disseminated to people with BD, highlighting difficulties in translation into practice.

### Development and piloting of the current intervention

Our international team of researchers, clinicians and consumers developed and piloted a novel, guided self-help web-based psychological intervention to improve QoL in late stage BD [8]. The low-intensity MBI is specifically tailored for late stage BD, drawing from Acceptance and Commitment Therapy (ACT), Mindfulness Based Cognitive Therapy (MBCT) and Compassion-focused Therapy (CFT). The intervention was originally named ORBIT (Online, Recovery-oriented, Bipolar Individualised Tool), but to keep participants unaware of the present trial’s hypothesised superior condition, ORBIT now refers to the project as a whole. For this report, the active intervention is titled ‘Mindfulness for Bipolar 2.0’ and the active control condition is titled ‘Psychoeducation for Bipolar’, but: to minimise expectancy effects, the names and key features of each arm are not mentioned in recruitment or consent processes.

Published pilot data suggests the first iteration of Mindfulness for Bipolar was feasible, safe and potentially effective in improving QoL [8]. No further published studies have investigated web-based MBIs specifically tailored for late stage BD. However, in related severe and chronic mental illness populations, there is support for the efficacy of generic MBIs and MBCT [26, 27], as well as ACT [28, 29]. Evidence suggests that those with chronic mental illness benefit from mindfulness strategies to mitigate the distressing effects of symptoms (via mindful acceptance of internal experiences), and improve self-concept (via promoting an experience of self as observer, moderating self-evaluations and encouraging commitment to valued goals despite symptoms) [30]. Indeed, there is evidence that those with a significant BD history may specifically benefit from a bipolar-tailored version of MBCT [15, 31, 32].

### The present project

Building on pilot study findings, we now describe the development of and protocol for a definitive RCT of the second iteration of the MBI (Mindfulness for Bipolar 2.0) for improving QoL in late stage BD.

The overarching aim of the present RCT is to assess the effectiveness and cost-effectiveness of a novel, web-based intervention in improving QoL in late stage BD vs. an active control.

#### The trial’s primary hypothesis

Relative to an active control (Psychoeducation for Bipolar), it is predicted that Mindfulness for Bipolar 2.0 will significantly improve QoL (baseline to endpoint change) on the Brief QoL.BD [33] immediately post-intervention. Data will additionally be collected at three and six months post-baseline, allowing examination of the trajectory of intervention effects over time.

#### Secondary hypotheses

It is anticipated that relative to Psychoeducation, the Mindfulness intervention will improve QoL across the full 6 months of the trial. A significant time X group assignment effect is therefore predicted. It is further anticipated that, relative to Psychoeducation, the Mindfulness condition will be associated with improvements in self-rated anxiety, self-rated depressive syndrome, observer rated depression, and attrition rates. Possible group differences will also be explored in a range of secondary outcomes for which directional predictions are not made: observer-rated manic symptoms; functional impairment; functionally oriented measure of QoL; sleep quality, social rhythm stability, and episode relapse (time to first). It is also anticipated that the Mindfulness condition will be more cost-effective than Psychoeducation. Potential moderators and mediators of treatment effects will also be explored as described below.

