
### Statistical analysis plan

Sample size was determined by power analysis using G*Power 3. Analyses were conducted on the primary endpoint (Brief QoL.BD score) at T1 relative to baseline. Based on our pilot study (intent-to-treat *d* = 0.52), and Brief QoL.BD change in comparable RCTs [22, 51], a between-group effect size of *d* = 0.4 was conservatively estimated. This small-to-moderate effect size is comparable to effect sizes found for adjunctive CBT on a range of outcomes in BD [78], and therefore can be considered a clinically important difference given the new intervention is low intensity, low cost, and high access. A sample size of 200 (100 in Mindfulness for Bipolar 2.0 and 100 in Psychoeducation for Bipolar) would provide at least 80% power (1-*β*) to detect an effect of this size at α = 0.05 (two-tailed). Attrition at immediate follow-up was conservatively estimated at 33% based on attrition rates in the pilot study and our earlier RCT of a web-based intervention for BD [39], so *N* = 300 randomised participants are required to generate the required sample size of 200 for the primary analysis.

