#### Time trend analysis of QoL

To investigate the secondary outcome of expected superiority of Mindfulness for QoL outcomes across the full 6 months of the trial, an intention to treat mixed model analysis using T0, T1, T2 and T3 QoL.BD scores will be undertaken.

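### The 6-month superiority hypothesis for QoL is tied to a time-by-group interaction, which has no direction and cannot by itself show superiority across 6 months

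*Protocol article*

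**What the plan says.** Under Secondary hypotheses, the protocol article expects that, relative to Psychoeducation, "the Mindfulness intervention will improve QoL across the full 6 months of the trial". The next sentence draws the statistical consequence: "A significant time X group assignment effect is therefore predicted".

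Under Time trend analysis of QoL, the aim is restated as "expected superiority of Mindfulness for QoL outcomes across the full 6 months of the trial", and the method is given as follows: "an intention to treat mixed model analysis using T0, T1, T2 and T3 QoL.BD scores will be undertaken". That section states neither how time is coded nor which treatment contrast carries the claim. The interaction is therefore the only criterion the document attaches to this hypothesis.

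The planning figures, under Statistical analysis plan, concern the primary T1 comparison only: an effect size of d = "0.4 was conservatively estimated", two-sided 5%, and 100 per arm analysed, which "would provide at least 80% power". No power is stated for the 6-month hypothesis.

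**The concern.** The hypothesis has a direction and a duration. An interaction over four visits with categorical time asks only whether the two mean profiles fail to be parallel. A benefit that appears at T1 and is held makes them non-parallel, because T0 is in the model. So does a benefit gone by T2, a reversal, or a lasting harm. If significance is taken as support, patterns that contradict the hypothesis count as readily as the one it describes.

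The test also spreads its sensitivity over three degrees of freedom when the hypothesis concerns one direction of departure. At stake is whether a secondary claim of 6-month superiority would rest on a result that answers that question.

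**Working it through.** **Inputs from the protocol.** d = 0.4, two-sided α = 0.05, 100 per arm analysed, 300 randomised, 33% attrition at T1, visits T0 to T3.

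**Assumptions not in the protocol.** 100 per arm at every visit; a within-person correlation ρ; compound symmetry, with AR(1) over visit order as a check; d scaled either to the SD of change or to the raw SD.

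**Step 1: the plan's own figure.** Power for T1 is approximately Φ(0.4 × √(100/2) − 1.96) = Φ(0.868) = 0.807, or 0.804 with the noncentral t. Also 300 × 0.67 = 201. The stated sample size reproduces.

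**Step 2: the interaction under compound symmetry.** The interaction is the joint test of the between-arm differences δ in change from T0 at T1, T2 and T3. In change-SD units these changes have variance 1 and covariance 0.5, so S = 0.5·I + 0.5·J and S⁻¹ = 2·(I − 0.25·J), where J is the all-ones matrix. The noncentrality is λ = δ′S⁻¹δ ÷ (2/100), on 3 df. The 1-df contrast averages the three changes; its variance factor is 0.5/3 + 0.5 = 0.667.

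| True differences (T1, T2, T3) | λ, 3 df | Interaction power | λ, 1 df | Average-change power |
|---|---|---|---|---|
| +0.4, +0.4, +0.4 | 0.24/0.02 = 12 | 0.84 | 0.16/0.667/0.02 = 12 | 0.93 |
| +0.4, 0, 0 | 0.24/0.02 = 12 | 0.84 | 0.0178/0.667/0.02 = 1.33 | 0.21 |
| −0.4, −0.4, −0.4 | 0.24/0.02 = 12 | 0.84 | 12 | 0.93, with negative sign |
| +0.4, 0, −0.4 | 0.64/0.02 = 32 | 0.999 | 0 | 0.05 |

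The first three rows have identical interaction power. The averaged contrast separates the first two by power and the third by the sign of its estimate.

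**Step 3: scaling of d.** If 0.4 is in raw SD and ρ = 0.6, the change variance is 2 × (1 − 0.6) = 0.8, so λ = 12/0.8 = 15: interaction 0.92, average change 0.97. At ρ = 0.3 on the same scale, λ = 12/1.4 = 8.57: 0.69 against 0.83. On the change-SD scale the result does not depend on ρ.

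**Step 4: AR(1), ρ from 0.3 to 0.7, d on the SD of the T0-to-T1 change.** For a sustained 0.4, interaction power is 0.67–0.75 and average-change power 0.73–0.86. For a T1-only 0.4, interaction power is 0.85–0.89. Here the interaction is more likely to be significant for the short-lived benefit than for the sustained one. Equal power for these two patterns is a feature of compound symmetry; equal power for benefit and harm holds under any covariance.

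**Step 5: cost of the extra degrees of freedom.** A noncentrality of 7.85 gives 80% power on 1 df and 64% on 3 df. To recover 80% on 3 df needs 10.90, and 10.90/7.85 = 1.39, so about 39% more information.

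**The case against.** The best defence is that the protocol predicts an interaction and does not say superiority will be declared on that p-value alone. The time trend section does not mention the interaction. With baseline in the model and arms equal at T0 by randomisation, greater improvement than control does appear as time by group. The primary hypothesis section also gives trajectory as a reason for the later visits. All of this stands, and it is a reason to keep the interaction as a description. It does not remove the inference the article itself draws from a directional hypothesis to a non-directional effect.

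Four stronger readings are tempting and do not hold.

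- A reader might infer that the average benefit will never be tested. The article leaves contrasts open and an unseen analysis plan may define one; it can only be said that the article names none.
- A reader might object that a linear slope would miss an early, sustained gain. The coding of time is not stated, so that criticises a choice the document does not make.
- A reader might infer that power is badly damaged, by setting 68% for the interaction against 94% for a baseline-adjusted average (0.3 SD, ρ = 0.6). That comparison changes two things at once. Given the same common baseline mean, the 3-df test reaches 84%. The effect of 0.3 SD is also smaller than the protocol's 0.4.
- A reader might fear a declared success when the average benefit is zero. The reversing profile shows what the test permits, but it needs equal benefit and harm, and the visit estimates would reveal it.

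An average over T1–T3 also does not prove durability. With a common baseline mean, ρ = 0.6 and 100 per arm, differences of 0.6, 0.3, 0 SD give 94% power, the same as a constant 0.3; differences of 0.6, 0, 0 still give 64%. This limit stands and shapes the fix.

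**Conclusion.** The point holds as a mismatch between hypothesis and test. The only criterion named for 6-month superiority is, with categorical time, a 3-df test without direction, and its significance does not establish that Mindfulness is superior across 6 months.

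The loss of power is secondary and moderate: at d = 0.4, 100 per arm and compound symmetry, about 84% against 93% (change SD) or 92% against 97% (raw SD, ρ = 0.6). These figures rest on assumed correlations and on full data at T2 and T3, for which the protocol gives no attrition figure; the low-correlation and AR(1) cases are lower for both tests. The interaction is not blind to a sustained benefit.

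This is a secondary hypothesis. The T1 comparison and the sample size of 300 are untouched. The change is worth making because it costs almost nothing.

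**What to change.** In Secondary hypotheses and Time trend analysis of QoL:

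1. State that the 6-month hypothesis is tested by one contrast from the same mixed model, with categorical time and a common baseline mean: the between-arm difference in Brief QoL.BD averaged over T1, T2 and T3, two-sided 5%, with estimate and confidence interval.
2. Report the T1, T2 and T3 differences with confidence intervals beside it, and claim benefit lasting to 6 months only if the T3 difference supports it.
3. Keep the time-by-group test as a description of trajectory, not as the criterion for superiority.

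Cost: wording only; the data and visits are unchanged, and the model needs only these settings stated. There are two small downsides. The average can be significant for a large early benefit that has faded by T3, which is why item 2 is needed. It is also less sensitive than the interaction to a benefit seen only at T1, but that pattern is not the one this hypothesis describes, and the primary analysis already addresses T1.

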## Method

This trial is conducted by an international multidisciplinary team of researchers and clinicians in Australia, Canada, USA and the UK. The study was reviewed and approved by Swinburne University of Technology Human Research Ethics Committee (2016/289). Trial objectives and protocol align with all aspects of Good Clinical Practice [34], the WHO Trial Registration Data Set (Version 1.2.1) and Standard Protocol Items: Recommendations for Interventional Trials (Additional file 1) guidelines [35]. The trial has been registered with ClinicalTrials.gov (NCT03197974). Any changes to this trial protocol will be described in this trial registry. Findings will be reported to the scientific community according to Consolidated Standards of Reporting Trials (CONSORT) eHEALTH criteria [36].

### Trial design

The trial is a prospective, parallel group, rater-blind, superiority RCT with a one-to-one allocation ratio comparing the Mindfulness for Bipolar 2.0 intervention with a structurally equivalent, validated and therapeutically credible active control condition (Psychoeducation for Bipolar). The primary endpoint is immediately post-treatment (upon completion of the 5-week intervention). Follow-up time points are at 3-months and 6-months. Both interventions are guided self-help, and not intended to replace treatment as usual. The study setting is online, and participation in both arms occurs through a secure server.

### Randomisation

Participants will be sequentially allocated to intervention arms using a one-to-one ratio by predetermined permuted block randomisation with a block size of 10. The permutation sequence within blocks will be randomly generated by SAS Version 9.4, overseen by an off-site statistician, and coded into the website so randomisation is automated and free of potential allocation bias. Participants are unaware of the primary hypothesis of the study, and have no prior knowledge of the two intervention types, but are unavoidably aware of the intervention to which they have been randomised. To reduce expectancy effects for superiority of the intervention over the control condition, the trial is framed as a comparison between two interventions designed to improve QoL. Assessors will remain unaware of treatment condition, and assessors who become aware of the treatment condition will, if possible, be replaced. Success in keeping assessors unaware of the treatment condition will be quantified by asking interviewers to guess allocation upon completion of the RCT, and assessing whether they can do so at greater than chance levels. Statistical analyses will be conducted blind to treatment allocation by an off-site statistician.

### Recruitment and assessment

The study will be administered and conducted through a single-site, with recruitment primarily via open social media sites (e.g., International Bipolar Foundation Facebook site). Recruitment will also be facilitated in four English-speaking countries via advertisements disseminated online through public and mental health sites and social media, listservs and traditional advertisements (offline) posted in clinical services.

As summarised in the flow diagram (see Fig. 1), individuals interested in participating will be invited to visit the study website (https://www.orbitonline.org/) where they can sign up, view and provide their consent to the participant information and consent form, provide their contact details (including details of their medical health professional), and respond to initial screening questions regarding eligibility (i.e., received a diagnosis of BD from a mental health professional, experienced 10 or more mood episodes).

